#### 7.3.4 PSG at 12 ± 1 months (*Screened Group* children)

- PSG
- Children Sleep Habits Sleep Questionnaire
- Parents' subjective sleep quality (PSQI, Epworth scale)
- PSG progress monitoring sheet

#### 7.3.5 PSG at 18 ± 1 months (*Screened Group* children)

- PSG
- Children Sleep Habits Sleep Questionnaire
- Parents' subjective sleep quality (PSQI, Epworth scale)
- PSG progress monitoring sheet

#### 7.3.6 Visit V2 at 24 ± 1 months (*Screened Group* children)

- Clinical examination
- Digestive symptoms
- ENT follow-up
- Blood test results if available (TSH, haemogram)
- Rehabilitation
- Investigator's judgment of sleep apnoea
- Apnoea observed by parents
- Medical and surgical treatments
- AEs

#### 7.3.7 PSG at 24 ± 1 months (*Screened Group* children)

- PSG
- Children Sleep Habits Sleep Questionnaire
- Parents' subjective sleep quality (PSQI, Epworth scale)
- PSG progress monitoring sheet

#### 7.3.8 PSG at 30 ± 1 months (*Screened Group* children)

- PSG
- Children Sleep Habits Sleep Questionnaire
- Parents' subjective sleep quality (PSQI, Epworth scale)
- PSG progress monitoring sheet

### 7.3.9 V3 end-of-study visit at 36 ± 1 months

- Clinical examination
- Documentation of psychomotor development
- Digestive symptoms
- ENT follow-up
- Ophthalmic follow-up
- Blood test results if available (TSH, haemogram)
- Rehabilitation
- Investigator's judgment of sleep apnoea
- Apnoea observed by parents
- Childcare arrangements
- Acquisition of toilet training skills at night yes/no
- Acquisition of toilet training skills during the day yes/no
- Neuropsychological tests: Griffiths III, VABS-II, BRIEF-P, CBCL-P
- Medical and surgical treatments
- AEs

For children in the *Standard Care Group*, this visit will be combined with the inclusion visit.

Signature of the informed consent by the legal representatives for the 5-year follow-up within 15 days of the 3-year visit.

### 7.3.10 PSG at 36 + 1 months

- PSG
- Children Sleep Habits Sleep Questionnaire
- Parents' subjective sleep quality (PSQI, Epworth scale)
- PSG progress monitoring sheet

### 7.3.11 Visit V4 at 5 years ± 2 months

Visit to the IJL for patients screened and treated in the *Screened Group* and *Standard Care Group*.

- Patient's characteristics (weight, height, BMI);
- Confounding factors in intellectual disability;
  - INSEE socio-professional categories;
  - Associated rehabilitation (speech therapy, physiotherapy, psychomotricity, palatal plate at the time of the visit);
  - Childcare, education;
  - Bilingualism;
  - Family history (number of brothers and sisters/rank in siblings).
- Clinical examination;

- Oral and phonatory apparatus;
  - Macroglossia, micrognathia, prognathism;
  - Tongue position;
  - Position of the lower jaw at rest;
  - Teething.
- Hearing and vision evaluation;
- Digestive symptoms?
- Blood test results if available (TSH, haemogram);
- Medical and surgical treatments for OSA;
- Major medical events: AEs and surgery related to ENT, neurological and cardiopulmonary systems.
- Neuropsychological tests: Griffiths III, VABS-II, BRIEF-P, CBCL-P, WPPSI-IV, semantic verbal fluency and the language section of the CBCL-P language proxy questionnaire.

#### 7.3.12 PSG at 5 years $\pm$ 2 months

- PSG performed as part of routine care at Necker-Enfants Malades Hospital for patients screened and treated in the *Screened Group* and *Standard Care Group*.
- Children Sleep Habits Sleep Questionnaire
- Parents' subjective sleep quality (PSQI, Epworth scale)
- PSG progress monitoring sheet

#### 7.3.13 Telephone calls every 2 months by the clinical research nurse (children *Screened Group*)

The CRN will contact the parents of the children concerned every 2 months to collect information on:

- Medical and surgical treatments
- Protocol-related AEs linked to ENT, neurological and cardiopulmonary systems (AEs)
- Associated rehabilitation (physiotherapy, psychomotor therapy, speech therapy, palatal plate, osteopathy, other)

The CRN can also be contacted by parents spontaneously by email or telephone. She will fill in a contact form for each contact:

- If the contact is an unsolicited email, the email will serve as the source document,
- If the contact is a telephone call, the CRN will fill in the form with the description, start date and end date of the AE, and the dosage, route of administration, indication, start date and end date of concomitant treatments. This telephone contact form will be used as a source document.

#### 7.3.14 Premature withdrawal from the study

Premature withdrawal from the study means that the patient stops participating in the research before completing the end-of-study visit at 3 years  $\pm$  1 month. Any subject may stop participating in the research at any time for any reason.

In case of premature withdrawal, the investigator should record the date and reason in the electronic case report form (e-CRF):

- Withdrawal of consent
- Procedure-related adverse effect
- Investigator's decision
- Relocation or inability to continue the study
- Refusal to carry out the PSG at 3 years or the neurocognitive and behavioural assessment
- Other (please specify)

In the event of a serious adverse effect occurring in a subject who has been prematurely withdrawn from the study, the adverse effect should be monitored until its resolution.

Patients who leave the study prematurely will not be replaced.

#### **7.4 Data collection**

CLINACT is responsible for data management.

The following data will be recorded on an electronic case report form (e-CRF):

- By the CRN of the IJL:
  - data from bi-monthly contacts (or spontaneous contacts on the part of the parents) between the CRN and the parents,
  - data from questionnaires on children's sleeping habits,
  - data from the parents' PSQI and Epworth questionnaires,
- By the investigators
  - data from consultations with parents at the IJL (annual consultations)
  - the AEs causality and severity will be completed and validated by the investigators
- By the sleep technician:
  - PSG data.
- By the neuropsychologist:
  - neurocognitive and behavioural test data

Data from the PSG and neurocognitive and behavioural tests will be considered as source data.

CLINFILE will be responsible for the development and maintenance of the e-CRF. This e-CRF will be developed from a paper CRF written by the IJL and reviewed by CLINACT. User access to the e-CRF will be restricted by an authentication system and rights management: each person involved in data management will have a user ID and a password that must not be shared. This tool is fully compliant with international regulations (FDA 21 CFR Part 11, GCP).

The data collected will be confidential and covered by medical confidentiality. Only the first letter of the patient's surname and first name will be included in the e-CRF. Only pseudonymised data will be collected. The patient number will consist of a 2-letter code (ET for the *Screened Group* and ST for the *Standard Care Group*) followed by 2 digits assigned in ascending order of inclusion.

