## **4.4 Secondary endpoints**

- To demonstrate that screening for OSA by PSG and its treatment if necessary is associated with improved behaviour; the mean total scores and sub-scores of the Vineland Adaptive Behaviour Scales, Second Edition (VABS-II), Behaviour Rating Inventory of Executive Function – Preschool (BRIEF-P) and Child Behaviour Checklist - Preschool (CBCL-P) at the age of 3 years will be compared between the groups.
- To show that OSA is less frequent and less severe in the screened children; the number of children with OSA at the age of 3 years and the mean apnoea-hypopnoea index (AHI) at the age of 3 will be compared between the 2 groups;
- To show the value of peripheral saturation,  $\pm$  nocturnal transcutaneous carbon dioxide,  $\pm$  actigraphy,  $\pm$  suprasternal pressure sensor in predicting the presence of OSA with PSG.

- Parents' subjective sleep quality assessed using the Pittsburgh Sleep Quality Index (PSQI) and the Epworth Sleepiness Scale, and the child's subjective sleep quality assessed using the Children Sleep Habits Sleep Questionnaire;
- Assessment of language at 5 years, by analysis of the Quotient of Development for the Language subscale (QDL) of the Griffiths III, by analysis of the raw scores of the Naming and Word Comprehension tests of the Wechsler Preschool and Primary Scale of Intelligence - Fourth Edition (WPPSI-IV), a verbal fluency task (number of words produced in one minute) and by the CBCL-P language proxy questionnaire (number of words produced in French and a foreign language).
- Assessment of cognitive functions, by analysing the Composite Global Executive (CGE) Score and scores on the Inhibitory Control, Flexibility and Emerging Metacognition Indices, as well as the scores of the different sub-domains within each index obtained from the BRIEF-P scale;
- Assessment of behaviour by analysing the mean total scores and sub-scores obtained on the CBCL-P proxy questionnaire and the VABS-II.
- Finally, the results obtained from the Griffiths III, the BRIEF-P and CBCL-P proxy questionnaires and the VABS-II at 5 years will be compared with the results obtained at 3 years.

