### **6.1 Polysomnography**

In PSG, breathing and sleep stages are recorded, and sleep quality is investigated via recordings of brain activity during sleep. It is used to diagnose OSA. All PSGs will be performed at the child's home, and the installation will be done by a sleep technician. This PSG will be carried out under conditions similar to those for PSG in hospitals, to ensure greater comfort for parents and their children.

The exam must be scheduled within the required time frame. If the PSG is unsuccessful, a 2nd PSG will be attempted in the child's home. If this 2nd attempt is unsuccessful, the child will have to spend a night at Necker-Enfants Malades Hospital in [name] unit to undergo PSG.

The following sensors will be installed:

- Elastic straps around the chest and stomach: these straps are used to record breathing by studying the movements of the rib cage and stomach;
- A microphone will be held in place at the base of the neck with surgical tape to record snoring and the flow of air through the throat;
- Another sensor fastened to the pyjamas will provide information on the child's position during sleep;
- A final sensor on the arm will provide information about the child's movements during sleep.

The following signals will also be recorded:

- Electroencephalography (EEG)
- Electromyography (EMG)
- Electrocardiography (ECG)
- Electrooculography (EOG)

Oxygen and carbon dioxide concentrations in the blood will be recorded via a sensor placed on the tip of the finger to measure oxygen concentration and a sensor on the ear or sole of the foot to measure carbon dioxide concentration. Measuring these two parameters will provide information on the impact of nocturnal breathing on gas exchanges.

[figure not shown]

This examination will be read and interpreted by the team at the Necker-Enfants Malades Hospital sleep centre. Depending on the results, treatment may be proposed by this team using the local practice, including ENT treatment (adenoidectomy and/or tonsillectomy) or CPAP treatment in the event of severe sleep breathing abnormalities and if ENT surgery is unsuccessful or not possible.

If OSA is detected at 30 months, ENT treatment and/or CPAP should be done no later than one month after screening, to allow a repeat check at 36 months and neuropsychological testing at 36 months  $\pm$  1 month after treatment and correction of OSA, for a duration of 5 months.

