All these treatments will be carried out at the Necker-Enfants Malades Hospital. A follow-up PSG will be performed to check that the sleep disorders have been corrected. This control PSG will be either a systematic PSG scheduled as part of the study, or an additional PSG for medical reasons. Other visits and/or hospitalisations may be necessary for medical reasons. In all cases, the schedule of one PSG every 6 months must be complied with.

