### **7.3 Visits and data collected**

Children in the *Screened Group*:

- They will be seen at a total of 4 visits, including a medical, neurocognitive and behavioural assessment at 3 years.
- They will benefit from 6 PSG performed at home by a sleep technician (or at the sleep unit at Necker-Enfants Malades Hospital in the event of 2 unsuccessful PSG at home).

During at-home PSG, the sleep technician will give parents:

- a questionnaire about the quality of their child's sleep
- 2 questionnaires about the quality of their sleep
- a monitoring sheet for the progress of the PSG

These questionnaires are to be completed by the parents and returned to the technician the following day.

The procedure for performing PSGs is described in the appendix of the protocol. This examination will be read and interpreted by the team at the Necker-Enfants Malades Hospital sleep centre. Depending on the results, treatment may be proposed by this team using the local practice, including ENT treatment (adenoidectomy and/or tonsillectomy) or CPAP treatment in the event of severe sleep breathing abnormalities and if ENT surgery is unsuccessful or not possible. All these treatments will be carried out at the Necker-Enfants Malades Hospital. A follow-up PSG will be performed to check that the sleep disorders have been corrected. This control PSG will be either a systematic PSG scheduled as part of the study, or an additional PSG for medical reasons. Other visits and/or hospitalisations may be necessary for medical reasons. In all cases, the schedule of one PSG every 6 months must be complied with. Treatments will be recorded throughout the follow-up.

- A clinical research nurse (CRN) from the IJL will make telephone calls every 2 months to the parents of the children taking part in this research to collect all the information on medical and surgical treatments and associated rehabilitation (physiotherapy, psychomotor therapy, speech therapy, palatal plate, osteopathy, etc.) received by the children, as well as any adverse events (AEs).

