## 11.5 PSG procedure

In PSG, breathing and sleep stages are recorded, and sleep quality is investigated via recordings of brain activity during sleep. It is used to diagnose OSA.

All PSGs will be carried out at the child's home, and installation will be carried out by a sleep technician. The exam must be scheduled within the required time frame.

The following sensors will be installed:

- Elastic straps around the chest and stomach: these straps are used to record breathing by studying the movements of the rib cage and stomach;
- A microphone will be held in place at the base of the neck with surgical tape to record snoring and the flow of air through the throat;
- Another sensor fastened to the pyjamas will provide information on the child's position during sleep;
- A final sensor on the arm will provide information about the child's movements during sleep.

The following signals will also be recorded:

- Electroencephalography (EEG)
- Electromyography (EMG)
- Electrocardiography (ECG)
- Electrooculography (EOG)

Oxygen and carbon dioxide concentrations in the blood will be recorded by a sensor placed on the tip of the finger for the oxygen concentration and a sensor on the ear or under the sole of the foot for the carbon dioxide concentration. Measuring these two parameters will provide information on the impact of nocturnal breathing on gas exchanges.

[figure not shown]

The sleep technician will give the parents a questionnaire for assessing the conditions under which the examination is carried out (home PSG monitoring form): he/she will have to record the child's height and weight on the day of the examination, based on available data (maximum 15 days old or measured on the day of the examination).

Parents must report any problems that arise during the night when the PSG is being performed on the monitoring form, using the items listed there.

The sleep technician will also give the parents questionnaires on the child's sleep quality (Children Sleep Habits Sleep Questionnaire) and the parents' sleep quality (PSQI) and Epworth Sleepiness Scale).

All these documents will be collected from the parents' home by the sleep technician the following day.

Recordings of the PSG, PtcCO2 and SpO2 will be loaded to Clinact's PSG tracking platform by the sleep technician and sent to [name] team for interpretation.

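### The 36-month PSGs behind the OSA-frequency and AHI comparison are read, with no masking described, by the team that treats the Screened children

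*Protocol*

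**What the plan says.** - **Endpoint.** Protocol section 4.4 compares between groups "the number of children with OSA at the age of 3 years and the mean apnoea-hypopnoea index (AHI) at the age of 3". It serves the objective in section 4.2 of showing less frequent and less severe OSA in the Screened Group.
- **Reader.** Sections 6.1 and 7.3: "This examination will be read and interpreted by the team at the Necker-Enfants Malades Hospital sleep centre". Section 11.5, which covers the study PSGs generally, says the recordings "will be loaded to Clinact's PSG tracking platform by the sleep technician and sent to" a team whose name is removed from the public copy. Section 6.1 identifies the readers as the Necker sleep centre.
- **Treatment.** Section 6.1: "Depending on the results, treatment may be proposed by this team using the local practice", and "All these treatments will be carried out at the Necker-Enfants Malades Hospital".
- **Check of treatment.** Section 6.1: "A follow-up PSG will be performed to check that the sleep disorders have been corrected". This control PSG may be one of the scheduled study PSGs.
- **Identifier.** Section 7.4: "The patient number will consist of a 2-letter code (ET for the *Screened Group* and ST for the *Standard Care Group".
- **Data entry.** Under section 11.5 the sleep technician enters both the PSG data and the reader's interpretation in the e-CRF.
- **Masking.** Section 7.1 calls the study open-label. No masked, recoded or second reading of the PSGs is described anywhere.

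**The concern.** AHI and the OSA call depend on a scorer's judgement of individual events. Here one team reads the PSG, proposes treatment from its own reading and checks whether the treatment worked. Its reading at 36 months is also the only described source of a between-group endpoint. Section 3.3 states that the unit aims at complete normalisation of sleep and already believes that early-treated infants do better.

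Open-label care does not force unmasked scoring, because a stored recording can be scored without its group. As the protocol stands, a difference in OSA frequency or mean AHI at 3 years could arise partly from how recordings were read. The data could not separate that from an effect of screening.

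**Working it through.** **1. What the reader can know**

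- By 36 months a Screened child has had up to five scheduled PSGs (6, 12, 18, 24 and 30 months) read by this team, and has been treated by it if OSA was found.
- A Standard Care child normally comes to it for a single study PSG (synopsis; section 7.3).
- The team can therefore recognise Screened children from its own files, whatever code the recording carries.

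**2. What the calendar reveals**

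Inputs: inclusion June 2017 to June 2019 (synopsis), both groups recruited in parallel (section 7.2), ages at inclusion (section 5.1), PSG timing (synopsis; section 7.1).

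- Latest Standard Care PSG: included June 2019, plus 1 month for the PSG, plus at most 3 months if home attempts fail. June 2019 + 4 months = October 2019.
- Earliest Screened 36-month PSG: included June 2017 at the oldest permitted age, 6 months, so 36 months of age is reached 30 months later, in December 2019. The 1-month early window in the synopsis gives November 2019.

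On the planned dates the two sets of readings do not overlap. Recording date identifies the group, and any drift in scoring over time falls wholly between the groups. The gap is only about a month, and section 7.1 lets the sponsor modify the inclusion period. An extension would create some overlap but would leave the sets largely sequential.

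**3. Group sizes**

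The protocol gives no figure for reader error. Its group sizes (section 9.1) are used below and reproduce.

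- Normal approximation: n = 2(1.96 + 0.84)² × 11.55² / 8² = 32.7, so 33.
- t-test: 33.7, so 34, with power 80.3% at 34.
- Attrition: 34 / 0.85 = 40.

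These numbers were set for Griffiths III, not for the PSG endpoint.

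**4. Illustration for OSA frequency**

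Assume no true difference, a Standard Care OSA frequency of 30%, 40% or 50% (section 3.1 gives 30-50% in children), and a reading shift that lowers the Screened frequency only. The test is the two-sided 5% uncorrected chi-squared test, z = (p1 − p2) / √(2p(1 − p)/n), where p is the pooled proportion. Rejection probabilities come from exact enumeration.

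| Shift in Screened Group | 30%, n = 34 / 40 | 40%, n = 34 / 40 | 50%, n = 34 / 40 | Range |
|---|---|---|---|---|
| 0 points | 5.4% / 4.8% | 5.3% / 5.2% | 4.5% / 5.7% | about 5% |
| 5 points | 8.0% / 7.8% | 7.7% / 7.5% | 6.4% / 8.1% | 6-8% |
| 10 points | 16.6% / 17.7% | 14.8% / 15.2% | 12.6% / 15.7% | 13-18% |
| 15 points | 32.9% / 36.6% | 27.5% / 29.4% | 24.0% / 28.6% | 24-37% |

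**5. Illustration for mean AHI**

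With an assumed downward shift of 0.2 SD in the Screened mean, the t-test rejects in 13-14% of trials. With 0.3 SD it rejects in 23-26% (n = 34 to 40).

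**The case against.** **The code.** A reader might infer that the group is printed on every recording. The protocol does not say so. Section 7.4 defines the patient number for study data, section 11.5 does not say which identifier a recording carries, and the technician rather than the reader makes the e-CRF entry. The code is a possible route only. The point does not depend on it, because recognition and recording date remain.

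**Direction.** A reader might infer that any bias favours screening. That is plausible but not shown. A team that aims at full normalisation could look harder for residual events in a treated child, which would work against the hypothesis.

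**Size.** A reader might assume opposite errors in both groups, so that 5-15 points each become a gap of 10-30 points. That needs under-calling in one group and equal over-calling in the other, for which the protocol gives no basis. Even then, 35% v 45% with 34 per group gives z = 0.10 / √(2 × 0.40 × 0.60 / 34) = 0.84, far from significance.

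**Origin of the study.** A reader might infer from section 10.8 that the treating unit initiated the research. That section describes one person in this way, and the sponsor is the Institut Jérôme Lejeune.

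**Silence.** A masked scoring could be set out in a document not shown, such as the data management plan of section 9.2. However, the protocol itself fixes who reads the recordings and how the reading is entered, and it describes no separate endpoint scoring.

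**Limits of masking.** A recording made on CPAP shows that the child is treated. Section 5.2 excludes children already on CPAP at inclusion and Standard Care children enter at 36 months, so such a recording most likely comes from the Screened Group. This limit stands. Masking still protects the remaining recordings.

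**Conclusion.** The concern holds for the secondary comparison of OSA frequency and mean AHI at 3 years. One team treats the Screened children and reads the endpoint PSGs with no masking described, and on the planned calendar recording date separates the groups.

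The size and direction of any shift are unknown. The false-positive rates of 6-8%, 13-18% and 24-37% rest on an assumed one-group shift of 5, 10 or 15 points with no true difference. They show sensitivity to reader bias and do not estimate it. The calendar argument rests on the planned inclusion dates.

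The documents do not support extending the point to the primary endpoint: the neuropsychologist enters the Griffiths III data, and PSG reading plays no part in that score. The sample size is also untouched. This is an inexpensive improvement that should be made, not a flaw in the main conclusion.

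**What to change.** 1. Give each PSG recording a group-neutral code and hold the group in a separate e-CRF field.
2. Leave the immediate reading for care as it is.
3. For the endpoint, have the existing sleep team score the stored 36-month recordings of both groups in one batch after the last is collected, in random order, with group, date and treatment history removed. Include recordings made in hospital after two failed home attempts. Section 11.5 describes upload by the sleep technician who visits the home and does not state it for hospital recordings, so their transfer should be specified.
4. Base AHI and OSA status for the comparison in section 4.4 on that scoring, under one rule fixed beforehand and applied identically to both groups.
5. Flag recordings made on CPAP as not fully maskable, and report how many there are by group.

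The cost is a coding step and the time to score at most 80 existing recordings a second time. No new recording, new reader, extra patient or change in care is needed.
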